## Abstract

**Background:**

Rheumatoid arthritis (RA) is a chronic, inflammatory rheumatic disease with the potential to induce significant disability. Patients with RA are at increased risk of cardiovascular diseases (CVD). Smokers with RA tend to experience more pain and fatigue, higher disease activity, more erosive joint destruction and a lower health-related quality of life (HR-QoL) than non-smokers. It remains to be determined whether these effects can be reduced by smoking cessation.

This randomised controlled trial (RCT) in patients with RA aims to examine the effect of intensive smoking cessation intervention (motivational counselling combined with tailored nicotine replacement therapy) versus standard care on smoking cessation, and consequently on disease activity. Secondary objectives are to explore the effect on flare, risk factors for CVD, lung function, physical function, HR-QoL, pain and fatigue in patients with RA.

**Methods:**

This will be a multicentre, open label, two arm, parallel group, RCT, including 150 daily smokers with RA, being in remission or having low-moderate disease activity (DAS28 ≤ 5.1). The intervention group (n = 75) will receive five counselling sessions with a trained smoking cessation counsellor based on the principles of motivational counselling. Furthermore, intervention patients will be offered nicotine replacement therapy tailored to individual needs. Participants randomised to the control group will receive standard care. The co-primary outcome is a hierarchical endpoint, which will be evaluated at 3 months follow-up and will include (1) self-reported smoking cessation biochemically validated by exhaled carbon monoxide and (2) achievement of EULAR clinical response (an improvement in DAS28 of > 0.6). Follow-up visits will be performed at 3, 6 and 12 months post-intervention.

**Discussion:**

This trial will reveal whether intensive smoking cessation counselling helps smokers with RA to achieve continuous smoking cessation and whether, as a concomitant benefit, it will reduce their RA disease activity. The trial aims to generate high quality evidence for the feasibility of a health promotion intervention for smokers with RA.

**Trial registration:**

ClinicalTrials.gov, identifier: NCT02901886. Registered on 10 September 2016. Recruitment status updated on 10th October 2016.

**Electronic supplementary material:**

The online version of this article (doi:10.1186/s13063-017-2309-5) contains supplementary material, which is available to authorized users.

## Background

Rheumatoid arthritis (RA) is a chronic inflammatory disease with a prevalence of 1% in the general population [1]. The onset of RA occurs at all ages, but most frequently in women aged 50–60 years [2]. The disease is not curable per se; however, its course can be improved significantly by use of disease-modifying anti-rheumatic drugs [3, 4]. All joints may be affected, but symptoms are most common in hands and feet. During periods of high disease activity, patients can experience severe pain and fatigue, which may restrict social life as well as physical and daily life activities [4, 5]. Furthermore, patients with RA have a reduced health-related quality of life (HR-QoL) [6, 7] and are at increased risk of cardiovascular diseases (CVD), with a risk comparable to that of patients with diabetes mellitus [8]. There is evidence that patients with RA have a 1.6-fold higher rate of acute myocardial infarction and ischemic stroke than patients without RA [9]. The inflammatory process in RA appears to be linked to the increased risk of CVD [10].

Smoking is more prevalent among Danish patients with RA than in the general population. A recent survey reported that 30% of patients with RA were daily smokers [11] compared to 17% in the general Danish population [12]. Tobacco smoking is a well-known environmental risk factor for the development of RA and the association is well established [5, 10, 13–16]. Furthermore, smoking is associated with chronic persistent RA [17]. Several studies suggest that smoking may augment symptoms associated with RA. Smokers with RA have a tendency to experience more pain and fatigue, higher disease activity, swifter radiographic progression and reduced HRQoL than non-smokers with RA [18–21].

Several strategies are available to support smoking cessation. A Cochrane review indicated that smoking cessation based on individual behavioural counselling combined with nicotine replacement therapy (NRT) is the most effective intervention for long-term smoking cessation in the general population [22]. The process of behavioural change is a central part of smoking cessation [23], and includes different stages as described in the Stages of Change Model [24]. Smokers embarking on smoking cessation will often move back and forth between various stages [25], which often last several years. Motivational interviewing has proven to be essential in behavioural counselling, and has assisted healthy people and those with chronic diseases to quit smoking [26–28]. Cessation counselling related to smoking, incorporating the principles of motivational interviewing, aims to encourage smokers to reflect on the pros and cons of smoking cessation and their motivation for, and self-efficacy in regard to, quitting this habit [29]. There is scarce evidence for the effect of smoking cessation interventions for patients with RA [30, 31]. In a non-controlled intervention study, 55 patients with RA received brief smoking cessation advice (3–5 minutes) from a rheumatologist followed by 20 minutes of verbal and written smoking cessation advice from a nurse [31]. Patients were additionally offered undefined pharmacological therapy. At 3 months follow-up, self-reported sustained smoking quit rates were 11.8%, indicating that smoking cessation among patients with inflammatory joint diseases may be achievable. The intervention that had the highest rate of smoking cessation was the combination of behavioural intervention and NRT [22]; however, this type of intervention has not been tested in a randomised controlled trial (RCT) among RA patients. Hence, an RCT to test such an approach versus standard care is urgently required for these patients.

Our hypothesis is that an intensive smoking cessation intervention will contribute to smoking cessation in patients with RA, which will then mediate a reduction in disease activity.

### Aim

This RCT in patients with RA aims to examine the effect of intensive smoking cessation intervention (motivational counselling combined with tailored NRT) versus standard care on smoking cessation, and consequently on disease activity. Secondary objectives are to explore the effect on flare, risk factors for CVD, lung function, physical function, HR-QoL, pain and fatigue in patients with RA.

## Methods/Design

### Trial design

The study is an international, multicentre, randomised trial in which daily smokers with RA in remission or with low-moderate disease activity ≤ 5.1 DAS28 (Disease Activity Score based on 28 joints assessment, serum-C-reactive protein (CRP) and patient’s Global assessment of a visual analogue scale (VAS)) will be randomised 1:1 to either an intervention group or to a control group. Patients will be followed for 58 weeks, including the 6-week intervention period and at 3, 6 and 12 months into the post-intervention follow-up period.

### Study sites

We will recruit patients from the Center for Rheumatology and Spine Diseases, Rigshospitalet, Denmark, and from the Preventive Cardio-Rheuma Clinic, Department of Rheumatology, Diakonhjemmet Hospital, Oslo, Norway.

### Characteristics of participants

#### Inclusion criteria

Patients will be included in the study if they have RA as defined by the American College of Rheumatology 1987 criteria and/or European League Against Rheumatism (EULAR) 2010 criteria [32, 33], are over 18 years of age, smoking tobacco daily, and are able to understand and speak Danish or Norwegian, respectively. Furthermore, for the 3 months prior to inclusion patients need to have been in clinical remission or low-moderate disease activity (DAS28 ≤ 5.1) and in stable anti-rheumatic medical treatment as documented in (1) the DANBIO registry in Denmark, or (2) the electronic patient journal, Department of Rheumatology, Diakonhjemmet Hospital, Oslo, Norway.

#### Exclusion criteria

Patients will be excluded from the study if they have had a change of dose or preparation in anti-rheumatic medical treatment within the previous 3 months, or a scheduled change in anti-rheumatic medical treatment, including glucocorticoid injection during the previous month, are cognitively or otherwise unable to give informed consent, are pregnant or breastfeeding.

### Recruitment, screening and enrolment

Screening for potentially eligible patients at each trial site will be carried out as follows:

At the Danish sites, potential participants will be recruited by one of the following methods:The DANBIO database, a nationwide registry including patients with inflammatory joint diseases in a longitudinal observational cohort [34], will be used to identify potential patients. Potential patients will be identified by using the search terms “rheumatoid arthritis” AND “smoker” (Fig. 1). Potentially eligible patients will receive an invitation to participate in the trial in a letter including written information about the trial and information about how the patient was identified in DANBIO. Three to four days after receiving the letter, the patient will be contacted by phone by the project manager ([name]) and invited to attend a meeting with a trained smoking cessation counsellor at which the trial will be further explained.

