**Fig. 1 Fig1:**
[figure not shown]
CONSORT Flow diagram: recruitment, screening and enrolmentAt routine visits to the rheumatology outpatient clinic. Potentially eligible patients will be orally informed about the trial and will subsequently receive written participant information.By referral from a physician or nurse from the rheumatology outpatient clinic. Potentially eligible patients will be orally informed about the trial and will subsequently receive written participant information.

The written participant information will contain information about the trial, background, objectives, course, measurements, and potential advantages and disadvantages for the patient. Furthermore, potential risks and adverse effects will be presented, and it will be stressed that participation is voluntary. Written informed consent will be obtained from each patient prior to inclusion in the trial.

At the Norwegian site, potential participants will be recruited as follows:At routine visits to the Preventive Cardio-Rheuma Clinic, Department of Rheumatology, Diakonhjemmet Hospital, Oslo, Norway. The information process will follow the same procedure as in Denmark.

Excluded patients, and eligible patients who do not want to participate, will be registered as either (1) not meeting the inclusion criteria, (2) refused to participate, or (3) excluded for other reasons.

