### Randomisation and blinding

Immediately after collecting baseline data using stratified block randomisation (block size 6–10) participants will be randomised to either (1) the intervention group or (2) the control group. The stratification variables are trial site and anti-cyclic citrullinated peptide (anti-CCP status). The allocation sequence is generated using computer-generated random numbers. Participants will be informed about their group allocation directly after randomisation. For participants randomised to the smoking cessation intervention group, the first intervention meeting will be scheduled as soon as possible, preferably immediately after randomisation. It is not possible either to blind participants to their allocated intervention or to blind the project nurses performing the intervention. The primary outcomes will be assessed by blinded assessors and smoking cessation will be self-reported by participants and validated biochemically.

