### Intervention and control group

#### Intervention group

The intervention includes (1) individual motivational counselling in combination with (2) tailored NRT.Individual motivational counsellingThe intervention consists of five individual motivational counselling sessions, each lasting 20–40 minutes over a period of 6 weeks with a trained smoking cessation counsellor. The principles of motivational counselling are based on the transtheoretical model of change [24]. The smoking cessation counsellor has also been trained in motivational counselling techniques specific to this intervention. Six registered nurses from the participating centres will provide the intervention. The Danish nurses have all completed the same Danish Cancer Society training programme based on the motivational counselling approach. The Norwegian nurses are specialised in pulmonary diseases and use the same counselling approach taught at the Danish Cancer Society.The smoking cessation counsellor’s role is to ask, listen and follow the participants cue and to adapt formal information to the participant’s motivational stage. Two tools, the ‘Line’ and the ‘Box’, will be used in the intervention. The Line is a simple tool to open the dialogue. It is constructed as a VAS scale and involves two questions which concern (1) the importance of smoking cessation and (2) the participant’s own belief in their capability of stopping smoking [40]. The Box consists of four empty squares, which the participant is asked to fill out. The Box helps the participant reflect and support the lifestyle change [40].Each meeting contains different themes. The first meeting is an introduction to the counselling course and preparation for smoking cessation, including the participant’s smoking status and their motivation for cessation. The second meeting aims to prepare the participant for the three first days without smoking. The third meeting aims to help the participant with issues concerning quitting smoking, including risk situations, relapse, reward and social network, and smoking cessation. The fourth meeting includes maintaining motivation, physical activity, handling of stress and mood swings. The fifth (final) meeting includes continuing help with smoking cessation and preparation for the time after the intervention.NRTThe participants in the intervention group will be offered NRT free of charge and, if accepted, it will be tailored individually according to the Fagerström Test for Nicotine Dependence [41]. Participants will be able to choose between the NRT products, including a patch, chewing gum, inhalator or mouth spray. The participants will note their tobacco and nicotine replacement consumption in a smoking diary.

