### Trial status

Recruitment for the trial started in October 2016 and is expected to be completed in October 2018.

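### On the DANBIO route candidates meet a smoking cessation counsellor before consent, and the same role delivers the open-label intervention: a possible, probably modest, selection bias on endpoint 1a that is cheap to remove

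*Protocol article*

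**What the plan says.** **Before consent.** Under Recruitment, screening and enrolment, Danish patients identified in DANBIO receive a letter, are phoned by the project manager and are "invited to attend a meeting with a trained smoking cessation counsellor at which the trial will be further explained". For the other two Danish routes (routine clinic visits, and referral by a clinic physician or nurse) patients are informed orally and in writing, and no counsellor is mentioned. Norwegian patients are recruited at routine visits, with the remark that "The information process will follow the same procedure as in Denmark".

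**Treatment.** Under Intervention group, there are five sessions, "each lasting 20–40 minutes over a period of 6 weeks with a trained smoking cessation counsellor". On staffing: "Six registered nurses from the participating centres will provide the intervention".

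**Allocation.** Under Randomisation and blinding, after baseline data and "using stratified block randomisation (block size 6–10) participants will be randomised" to the two arms; the strata are trial site and anti-CCP status. "Participants will be informed about their group allocation directly after randomisation", and the first counselling session should preferably follow at once. Neither participants nor intervention nurses are blinded.

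**Comparator.** Under Control group – standard care, controls receive usual outpatient care. Those who express an interest in counselling are told about municipal programmes.

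**Timing.** Under Trial status: "Recruitment for the trial started in October 2016 and is expected to be completed in October 2018".

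**The concern.** The article places the treating role upstream of randomisation. This is a stated assignment of tasks and not merely a concealment detail left out of a condensed text.

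A counsellor learns who was allocated to the intervention, because those patients come for sessions. Under blocked 1:1 allocation, earlier assignments carry information about the next one. Any daily smoker meeting the disease criteria is eligible, whatever his or her readiness to quit, and counsellors are trained to explore motivation. If more motivated candidates were encouraged when an intervention slot looked likely, the arms would differ in readiness to quit. The planned adjustment for baseline value, hospital and anti-CCP status would not correct this.

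Endpoint 1a (validated continuous cessation at 3 months) would be affected directly. Because 1b (DAS28 response) is tested only if 1a is significant, an error on 1a carries forward.

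A second, separate effect runs the other way. Future controls who come through this route meet a smoking cessation counsellor face to face, which is not part of the comparator as described and could dilute the contrast.

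**Working it through.** **The plan's own figures.** The article gives no guess rate. Its sample sizes reproduce with the usual two-proportion formula (two-sided 0.05, pooled variance under the null, no continuity correction): 26 per arm for 50% v 10% (power 90.7%), 65 per arm for 40% v 15% (90.0%), and 49 per arm, 98 in total, for the fallback (80.1%). They are not in dispute.

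**Ceiling on guessing.** Suppose the recruiter knows every earlier allocation in the stratum and always guesses the arm that is behind, tossing a coin when level (the Blackwell–Hodges convergence strategy). For a block of size 2m the expected share correct is

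[m + (2^(2m) / C(2m, m) − 1) / 2] / (2m)

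- Size 6: [3 + (64/20 − 1)/2]/6 = 4.10/6 = 68.3%
- Size 8: [4 + (256/70 − 1)/2]/8 = 5.33/8 = 66.6%
- Size 10: [5 + (1024/252 − 1)/2]/10 = 6.53/10 = 65.3%

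A simulation of 150 patients with sizes 6, 8 and 10 mixed gives 65.8% with two sites and 65.4% with three. Assumed, not in the article: an 80/20 split for two sites, 70% anti-CCP positive, and equal use of the three sizes.

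**Partial knowledge.** The same two-site simulation gives the lower rates below. The bias on 1a follows from

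bias = (2g − 1) × s × Δ

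where g is the guess rate, s is the shift in the motivated share between predicted-intervention and predicted-control slots, and Δ is the quit-rate gap between motivated and unmotivated smokers. The article gives neither s nor Δ; s = 0.25 to 0.50 and Δ = 30 points are assumed. The type I error takes a 10% quit rate in both arms, no true effect and 75 per arm, so SE = √(2 × 0.1 × 0.9/75) = 4.9 points.

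| What the recruiter knows | g | Bias on 1a (points) | Two-sided type I error |
|---|---|---|---|
| Every earlier allocation in the stratum (ceiling) | about 66% | 2.4–4.8 | 7.8–16.5% |
| Site balance only, anti-CCP unknown | 61.1% | 1.7–3.3 | 6.3–10.4% |
| Trial-wide balance only | 57.8% | 1.2–2.3 | 5.7–7.7% |
| Half of earlier allocations | 54.3% | 0.6–1.3 | 5.2–5.8% |
| One in six of earlier allocations | 51.8% | 0.3–0.5 | 5.0–5.1% |

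Example for the second row: (2 × 0.611 − 1) × 0.25 × 30 = 1.7 points, or 0.34 SE. The last row is a crude stand-in for one of six nurses who do not share information.

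**Is the upper end feasible?** With a 10% overall quit rate and Δ = 30 points, the motivated share cannot exceed 10/30, one third. With predicted slots split evenly, s = 0.50 needs a share of at least 25%. Unmotivated smokers would then quit at only 0–2.5%, and the motivated share would have to swing from 0–8% in one kind of slot to 50–58% in the other. That is barely plausible, so the upper limits should be read as extremes.

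**The case against.** The strongest reply has four parts.

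1. *The overlap is inferred.* No sentence says that the person in the information meeting also treats trial patients. The meeting is explicit for one of three Danish routes only. The Norwegian sentence may refer just to the oral and written information described immediately before it. All of this stands, and the point is limited accordingly. But the role title is the same and nothing separates the tasks.

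2. *Steering is not shown.* The counsellor explains the trial; the article gives that person no say over who is enrolled or when. This stands. The risk arises from the position of the meeting, not from any reported conduct.

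3. *Two in three is a ceiling.* A reader might infer that the next assignment can in practice be guessed that often, with type I error of 8–16%. The article does not support this. It would take one recruiter with the full allocation history of the stratum and the candidate's anti-CCP status, while delivery is spread over six nurses at different centres.

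4. *Block sizes and list-keeping.* A reader might also infer that printing the range 6–10 while recruitment was open is what makes the sequence guessable. It is not. The convergence guess needs only the running imbalance, so hiding or varying the sizes does not lower it; even blocks of 20 would leave a fully informed recruiter at 61.7%. Known sizes matter for certainty near a block's end, and would do so mainly if one fixed size were used (25%, 20% or 17% of assignments certain for 6, 8 or 10); a range already reads as varied. Who holds the list is a detail that an article may leave to the full protocol, so its absence is no finding.

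It is also fair to say that counsellor contact for controls would shrink the difference and not inflate it, and that the Discussion already concedes that taking part may motivate controls to quit.

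**Conclusion.** The point holds as a design weakness of limited size. On the DANBIO route, and possibly in Norway, the role that delivers an unblinded treatment meets candidates before consent, under small stratified blocks. Guessing could reach about 65–68% with complete knowledge and would be about 52–61% with partial knowledge. On the assumed s and Δ, the partial-knowledge bias on 1a is about 0.3 to 3.3 percentage points, with type I error of about 5–10%.

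This could not create the planned 40-point difference (50% v 10%). It would matter if the true effect were small or nil, because 1a is half of the primary endpoint and the gate to 1b. The effect of counsellor contact on controls goes in the opposite direction, and the documents do not allow the two to be netted. Since selection at enrolment cannot be repaired in the analysis and the remedy is cheap, the change is worth making for the recruitment that remained.

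**What to change.** In Recruitment, screening and enrolment, replace the counsellor in the pre-consent meeting with existing staff who meet two conditions: they do not deliver the counselling, and they do not know earlier allocations. The outpatient-clinic physicians or nurses who already refer patients are one possibility. The project manager, who already phones candidates, is suitable only if kept unaware of earlier allocations. The same staff should handle enrolment. State whether the Norwegian site follows the same rule.

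Introduce the counsellor only after randomisation and only to intervention patients. This fits the existing wish to start the first session straight after randomisation, and keeps the control group's contact in line with the standard care described.

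No change to block sizes and no regenerated allocation list is needed for this point, since neither lowers the guess rate.

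Cost: a transfer of tasks between existing staff, with no new visits or personnel. The small downside is that those staff take over some information meetings. In an open-label trial clinic staff may still hear of single allocations, but scattered knowledge of that kind leaves guessing close to chance, as the last rows of the table show.
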